### Baseline and Follow-up Clinic Examinations

Patients will undergo an initial baseline clinic examination, during which clinical measurements, demographic data, and past medical histories will be collected and electrocardiogram exams and biological examinations will be conducted.

A validated blood pressure monitor (ROSSMAX X3; Rossmax Swiss GmbH) will be used for blood pressure measurements. After 1 month, a satisfaction questionnaire—the Medical Outcomes Study Short Form-12 questionnaire [12]—will be completed by participants, so that we can assess their quality of life.

Twenty-four–hour ambulatory blood pressure monitoring (ABPM) will be performed for all included patients to analyze their blood pressure profiles through the use of a Holter monitor (Contec ABPM 50; Contec Medical Systems). Ambulatory blood pressure measurements will be scheduled to acquire a blood pressure reading every 30 minutes from 6 AM to 10 PM and every 60 minutes from 10 PM to 6 AM. The cuff will be placed on participants’ nondominant arms. Of the 48 possible measurements, at least 32 (67%) must be available. Otherwise, ABPM will be repeated. The Holter monitor must not get wet (eg, via a swimming pool, bath, or shower), and usual activities must be maintained. After installing the Holter monitor, study participants can return to their usual activities. They will be invited to return to the clinic 24 hours later, so that we can collect the data from their monitors. The results will be interpreted by a cardiologist.

Randomization will take place 1 month after participants’ inclusion, that is, after the collection of at least 32 interpretable ABPM measurements. All patients will be asked to attend 2 follow-up clinics within 6 months. The clinical follow-up data to be collected are detailed in Table 1.

**Table 1 table1:** Timetable for patient data collection throughout the trial.

Collected data	Baseline (inclusion visit)	After 29 days (1 day prior to the randomization visit)	After 3 months (follow-up visit 1)	After 6 months (follow-up visit 2)
Sociodemographics	✓			
Past medical history	✓			
Clinical examination^a^	✓	✓	✓	✓
Biological tests^b^	✓		✓	✓
ECG^c^	✓	✓		✓
SF-12^d^		✓		✓
ABPM^e^		✓		✓
Treatment compliance		✓	✓	✓
Side effects		✓	✓	✓

^a^The clinical examination will mainly include the assessment of blood pressure (systolic and diastolic blood pressure), BMI, and heart failure New York Heart Association stage.

^b^Biological tests will include those for serum creatinine, glycemia, lipid profiles, and brain natriuretic peptides.

^c^ECG: electrocardiogram.

^d^SF-12: 12-Item Short Form Survey.

^e^ABPM: ambulatory blood pressure monitoring.

### Randomization

Patients who meet the eligibility criteria will be randomly assigned to either of the study groups in a 1:1 ratio via the use of an interactive web responsive system.

The study groups are as follows:

Usual care group (control group): patients in this group will receive their antihypertensive treatment according to the usual approach during each consultation appointment made with the attending physicians.Telemonitoring group (intervention group): patients in this group will receive their usual care along with at-home self-monitoring, telemonitoring, and the titration of antihypertensive treatment.

### Intervention

#### Control Group

Participants randomized to the control group will receive usual care (ie, physician visits every 3-6 months and therapy according to standard treatment guidelines). In contrast to the intervention group, control group participants will not receive phone calls for therapeutic education, a treatment compliance assessment, treatment titration, or a side effect check. In cases of any worsening symptoms, patients will have to contact their general physician individually and independently.

#### Intervention Group

Participants randomized to the intervention group will receive therapeutic education, including information on diet, sleep, physical activity, and other lifestyle advice, from the research associate. Patients will also be provided with a validated blood pressure monitor (ROSSMAX X3), and they will be taught how to use the blood pressure monitor at home. Patients will be asked to measure their blood pressure 3 times in the morning and 3 times in the evening for 3 days per week.

Once per week, the research associate will call the patients to check their treatment compliance and verbally collect the blood pressure measurements. Compliance evaluation will be conducted by asking the patients whether they have been taking their medication correctly every day on time for the past week. Patients will be asked to keep their empty treatment boxes. The remaining pills will be counted, and patient compliance will be assessed. The research associate will also remind patients about lifestyle and dietary measures. Subsequently, the research assistant will fill in the data entry fields in the electronic platform, which can be checked and validated by the investigators. Patients will be contacted every month via telephone by their attending physician for 6 months to titrate the antihypertensive treatment according to the data collected by the research associate. At day 90 and day 180, the medical visit will be conducted face-to-face. For the titration of antihypertensive medicines, the decision criterion will be the percentage of home blood pressure readings that meet the target. If at least 75% (375/500) of the readings since the last visit meet the blood pressure target, no changes in treatment will be considered. If less than 75% (375/500) of the readings meet the target, we will recommend readjusting the treatment. During the telephone follow-up calls, physicians will encourage participants to adhere to the treatment. Regardless of blood pressure control, if patients experience side effects, the involved antihypertensive drug will be stopped or changed, or its dose will be reduced.

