**Methods:**

Our trial will be a prospective, rater-blinded randomized controlled trial carried out with primary care physicians in the Sahel region of Tunisia. Patients will be eligible for enrollment if they are aged over 35 years, are newly diagnosed with hypertension, or are known to be poorly controlled on antihypertensive therapy. Participants will be randomly assigned in a 1:1 ratio to the telemonitoring arm or usual care arm. The telemonitoring arm will involve a weekly telephone call for the collection of the home blood pressure measurements, therapeutic education, and treatment compliance assessment as well as a monthly call for treatment titration and a side effect check. Randomization will be done via the use of an interactive web responsive system, and patients will be stratified by investigation center. Neither participants nor investigators will be masked to the group assignments. The primary outcome will be the change in mean 24-hour systolic blood pressure from baseline to the 6-month follow-up in the 2 groups. All randomized patients who attend the follow-up visit at 6 months and have no missing data for the primary outcome will be included in the analysis.

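### The only compliance method described (pill count, kept boxes, weekly questioning) belongs to the telemonitoring arm, so the >80% compliance and adverse-effect comparisons are at risk of differential ascertainment

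*Protocol article*

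**What the plan says.** **Telemonitoring arm.** The Intervention Group section sets out a weekly contact: "Once per week, the research associate will call the patients to check their treatment compliance and verbally collect the blood pressure measurements". The method at that contact is self-report: "Compliance evaluation will be conducted by asking the patients whether they have been taking their medication correctly every day on time for the past week". The section then adds a quantity measure: "Patients will be asked to keep their empty treatment boxes. The remaining pills will be counted, and patient compliance will be assessed". The Abstract (Methods) gives this arm "a monthly call for treatment titration and a side effect check".

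**Control arm.** The Control Group section says that "control group participants will not receive phone calls for therapeutic education, a treatment compliance assessment, treatment titration, or a side effect check". Between visits, reporting is left to the patient: "In cases of any worsening symptoms, patients will have to contact their general physician individually and independently". Usual care is described as "physician visits every 3-6 months and therapy according to standard treatment guidelines".

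**Both arms.** Under Baseline and Follow-up Clinic Examinations, "All patients will be asked to attend 2 follow-up clinics within 6 months". Table 1 in that section ticks treatment compliance and side effects at day 29 (the day before the randomization visit), month 3 and month 6, with no split by arm. It has no row for hospitalizations or emergency admissions.

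**Use of the data.** Secondary Outcomes includes the percentage of patients taking more than 80% of their antihypertensive medication at 6 months, and clinical outcomes covering hospitalizations, emergency admissions and adverse effects. Research Questions makes compliance part of the first main question and cardiovascular complications the third. Study Design leaves participants and investigators unmasked; only the cardiologist who reads the primary outcome is blinded.

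**The concern.** An outcome defined as more than 80% of medication taken needs a quantity measure. The only one in the article is a pill count, which depends on patients having kept their boxes, and that instruction appears only for the telemonitoring arm. If the text is followed as written, a control patient reaches month 6 with no boxes to count, and compliance must be judged in some other way.

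Side effects raise a similar problem. Telemonitoring patients are asked about them monthly. Control patients have the scheduled visits and whatever they report unprompted. If everything recorded is pooled into one adverse-effect comparison, the arms differ in how often they were asked.

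At stake are one part of the first main research question and the safety comparison. Both are assessed by people who know the allocation. A box that was never kept cannot be counted later, so no analysis plan can repair this after the fact.

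**Working it through.** **Step 1: set the provisions side by side.**

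| Item | Telemonitoring | Control | Common schedule (Table 1) |
|---|---|---|---|
| Compliance by self-report | Weekly call | No call | Ticked at day 29, months 3 and 6; method not given |
| Boxes kept, pills counted | Described | Not described | Method not given |
| Side effects | Monthly call | No call; patient-initiated contact if symptoms worsen | Ticked at day 29, months 3 and 6; method not given |
| Hospitalizations, emergency admissions | No method described | No method described | No row |

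The first three rows show a difference between arms that the common schedule does not remove, because a shared visit date does not make the instrument the same. The last row shows a gap common to both arms, not a difference between them.

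**Step 2: how much a difference in instrument could matter.** The plan gives no figure on this point, so there is none to reproduce. The calculation below is an illustration.

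Inputs from the article: 230 recruited per group and 15% dropout (Sample Size); significance at P<.05 (Statistical Analysis), taken as two-sided. Completers per arm: 230 × 0.85 = 195.5, taken as n = 195.

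Assumptions, not in the article: the true proportion above 80% compliance is the same in both arms, p₁ between 0.40 and 0.70; the instrument alone raises the recorded proportion in one arm to p₂ = p₁ + 0.05, 0.10 or 0.15.

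Probability of a significant result, normal approximation for two proportions:

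Φ[(|p₂ − p₁| − 1.96 × SE₀) / SE₁], with SE₀ = √(2p̄(1 − p̄)/n), p̄ = (p₁ + p₂)/2, and SE₁ = √(p₁(1 − p₁)/n + p₂(1 − p₂)/n).

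Example, p₁ = 0.60 and p₂ = 0.70:
- SE₀ = √(2 × 0.65 × 0.35/195) = 0.0483
- SE₁ = √(0.24/195 + 0.21/195) = 0.0480
- (0.10 − 1.96 × 0.0483)/0.0480 = 0.11, and Φ(0.11) = 0.54

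| True rate in both arms | Shift 5 points | Shift 10 points | Shift 15 points |
|---|---|---|---|
| 40% | 17% | 51% | 85% |
| 60% | 17% | 54% | 89% |
| 70% | 20% | 63% | 95% |

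With no shift the figure would be 5%. The formula uses the absolute difference, so the same pair of recorded rates gives the same probability whichever arm is the higher.

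**Step 3: direction.** Repeated self-report to the person delivering the programme could raise recorded compliance in the telemonitoring arm. A count of returned pills could instead reveal missed doses that a control patient's answer at a visit would not. More frequent questioning would tend to raise recorded side effects in the telemonitoring arm. The documents do not settle the net direction.

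**The case against.** The strongest reply is that a common, arm-neutral assessment is already planned. Table 1 ticks compliance and side effects at day 29, before any patient has an arm, and repeats them at months 3 and 6 for everyone. The compliance outcome is tied to the 6-month follow-up. The weekly question covers only the past week and cannot by itself give a percentage of medication taken. Nothing says that call data enter the endpoints. The calls are also the treatment under test, so unequal contact is inherent in the comparison. Finally, the article condenses a fuller protocol, where visit procedures may be spelled out.

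Much of this stands. Unequal contact is not itself an error. If the endpoints used only the common visits and one method, most of the asymmetry would go.

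It does not dispose of the point. Table 1 says when, not how. The article is not merely silent on method: it gives one and places it under the intervention arm. Nor does it separate contact made as treatment from contact made to measure an endpoint.

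Two stronger readings are tempting. A reader might infer that these comparisons are biased. The text supports only a risk, because it does not say which data feed the endpoints. A reader might also infer that the calls capture hospitalizations and emergency visits more completely in the telemonitoring arm. The article does not describe any call as asking about them, so no ratio of capture between arms can be derived. The gap there is that no collection method is stated for either arm.

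**Conclusion.** The point holds as a risk of differential ascertainment in two secondary comparisons: the >80% compliance outcome and adverse effects. The asymmetry between arms is in the text; its effect on the endpoints is not established, and its direction cannot be fixed in advance. The rates of 17-20%, 51-63% and 85-95% rest entirely on assumed shifts of 5, 10 and 15 points. They show that a modest instrumental difference would matter at this sample size, not that one of that size exists. The primary outcome, 24-hour ambulatory pressure recorded in all patients and read by a blinded cardiologist, is unaffected. The change is worth making because compliance is part of a main research question and the remedy is cheap, but the trial's main conclusion does not depend on it.

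**What to change.** - **Compliance.** Ask both arms to keep all boxes and bring them, with remaining pills, to the 3- and 6-month visits already scheduled. Derive the >80% outcome only from that visit pill count. Weekly self-report then serves the intervention and does not enter the endpoint.
- **Adverse effects.** Compare arms using only what the same structured question elicits at those two visits. Report side effects found through calls separately, as telemonitoring-arm safety data.
- **Hospitalizations and emergency admissions.** Add them to Table 1 and to the same visit question in both arms.

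The cost is protocol and case report form wording, plus a pill count at existing visits. There are two downsides. Asking control patients to bring boxes may slightly raise their compliance. Events that patients do not recall at a visit will be left out of the between-arm comparison.

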### Target Blood Pressure

The target blood pressure will be based on the 2018 European Society of Cardiology and European Society of Hypertension Guidelines [13].

The home blood pressure target will be ≤135/85 mm Hg, and the general practitioners’ office blood pressure target will be ≤140/90 mm Hg. The mean ambulatory blood pressure targets will be ≤135/85 mm Hg at daytime, ≤120/70 mm Hg at nighttime, and ≤130/80 mm Hg for 24 hours.

### Statistical Analysis

Categorical variables will be expressed as frequencies and percentages, while continuous variables will be expressed as means with SDs. An analysis of variance will be performed to compare the two study groups in terms of the primary end point. The normality of continuous data will be assessed with the Shapiro-Wilk test. Furthermore, we will use a general linear model for repeated measures to compare the marginal means of Gaussian quantitative dependent variables before and after the intervention (a Bonferroni test will be considered). A nonparametric test (the Friedman test) will be used for the comparison of non-Gaussian quantitative variables before and after intervention. The Cochran Q test will be performed to compare binary dependent variables before and after intervention. Subgroup analyses will be performed by age (<65 years and ≥65 years), sex, and the severity of hypertension. Differences between continuous variables will be evaluated with a 2-tailed Student *t* test or by its correction, as appropriate. The differences among the categorical variables will be evaluated with the Pearson chi-square test. All tests will be considered significant at the cutoff value of *P*<.05.

Data will be collected via an electronic data capture system (Dacima Clinical Suite; Dacima Software Inc) that is compliant with international data security requirements (ie, those of the US Food and Drug Administration [FDA] Title 21 of the Code of Federal Regulation [CFR], part 11; Health Insurance Portability and Accountability Act [HIPAA]; International Council for Harmonisation of Technical Requirements for Pharmaceuticals for Human Use [ICH]; and General Data Protection Regulation [GDPR]). Dacima Clinical Suite is authorized by the local body of personal data protection. The electronic case report form will be used to perform quality checks on the data (checks on simple controls [eg, range check], eligibility criteria, and complex controls) to increase the accuracy of the data. Double data entry will not be scheduled, as data will be directly captured in the electronic data system. Investigators and research assistants will use monitoring data tools as an audit trail for tracking the data modification log, data queries, and electronic signatures. Research assistants will use source document verification tools to ensure the accuracy of the collected data. Automatic alerts will be implemented to notify the responsible investigator about any data or protocol violations.

Participants who do not have data on the primary outcome at the 6-month follow-up assessment will be labeled as those who are missing data for the primary outcome at this time point. A further sensitivity analysis will include participants with 1 missing measurement. The frequency (percentage) of losses to follow-up (defaulters and withdrawals) after 6 months will be reported by randomized group and compared between the two groups. The availability of the outcome data for the primary and secondary outcomes will be summarized for the two randomized groups. The mixed-effects model implicitly accounts for data missing at random; however, the missing data mechanism will be explored. A logistic regression model will be used to explore any associations between baseline characteristics and the availability of data on the primary outcome. Any changes to the assumptions made in the primary analysis (ie, data missing at random) will be considered in a sensitivity analysis.

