**Results:**

Recruitment to the trial started in July 2020. The study was initiated with 17 primary care physicians. We expect the inclusion period to last for approximately 6 months. We expect to complete data collection by the end of 2021 and plan to disseminate the results subsequently.

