## Methods

### Study Design

Our trial will be a multicentric, rater-blinded, prospective randomized controlled trial. The allocation ratio between the intervention and control group will be 1:1. Randomization will be done via the use of an interactive web responsive system, and patients will be stratified by investigation center. Neither participants nor investigators will be masked to the group assignments. However, the cardiologist, who will interpret the results of the primary outcome, will be blinded.

The study is expected to last for an overall duration of 12 months (from the first patient who is enrolled to the last patient who completes the trial). The recruitment period will last for 6 months, and the follow-up interval will be 6 months.

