### Outcomes

#### Primary Outcome

Our primary outcome will be the percentage of patients who exhibit a change of 10 mm Hg in average 24-hour SBP from baseline to the 6-month follow-up.

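### The primary analysis of variance names neither baseline 24-hour SBP nor centre, which gives up precision but does not bias the comparison

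*Protocol article*

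**What the plan says.** The method for the primary end point is one sentence in the Statistical Analysis section: "An analysis of variance will be performed to compare the two study groups in terms of the primary end point". No baseline value, centre term or other covariate is attached to it there or elsewhere in the article. The other between-group methods in that section, the Student t test and the Pearson chi-square test, also come without covariates.

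The design supplies two natural adjustment variables:

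- **Centre.** Study Design and the Abstract both say that "patients will be stratified by investigation center". The Abstract adds: "The study was initiated with 17 primary care physicians". The number of centres is not given.
- **Baseline 24-hour SBP.** Baseline and Follow-up Clinic Examinations says that 24-hour "ambulatory blood pressure monitoring (ABPM) will be performed for all included patients", and that randomisation happens only "after the collection of at least 32 interpretable ABPM measurements". Table 1 schedules this recording at day 29, the day before the randomisation visit, and again at 6 months.

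Two further statements affect how the ANOVA sentence is read. The Statistical Analysis section later says: "The mixed-effects model implicitly accounts for data missing at random; however, the missing data mechanism will be explored", without defining that model. The primary outcome is also given in two forms. The Abstract says: "The primary outcome will be the change in mean 24-hour systolic blood pressure from baseline to the 6-month follow-up in the 2 groups". The Primary Outcome section makes it "the percentage of patients who exhibit a change of 10 mm Hg in average 24-hour SBP from baseline to the 6-month follow-up".

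**The concern.** A two-group ANOVA on change, with no other term, is the same test as a two-sample t test on change. A change score uses the baseline, but with a fixed coefficient of 1. When baseline and follow-up are imperfectly correlated, that coefficient is not the most efficient one, and regression on the baseline gives a smaller variance. The stratification factor is also left out, so between-centre variation stays in the error term although randomisation has balanced it across arms.

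Patients enter either newly diagnosed or poorly controlled on treatment, and Strengths and Limitations accepts that their clinical profiles may differ greatly. Baseline pressure is therefore likely to carry useful information. What is at stake is the width of the confidence interval and agreement between analysis and design, using data that the trial collects anyway.

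**Working it through.** **Inputs from the documents.** Difference 5 mm Hg, SD 15 mm Hg, 80% power, 199 per group, 15% dropout, 230 recruited per group (Sample Size); significance at 0.05 and a two-tailed t test (Statistical Analysis); 1:1 allocation (Study Design). **Assumed, because the documents give no value:** the correlation rho between baseline and month-6 24-hour SBP, 0.3 to 0.8; the share of variance between centres (ICC), 0.01 to 0.10.

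**Step 1: the plan's own figure.** n per group = 2 × SD² × (1.960 + 0.842)² / difference² = 2 × 225 × 7.849 / 25 = 141.3, so 142 (143 with the t distribution), not 199. With SD 15 for the reduction, 199 per group gives 5 / (15 × √(2/199)) = 3.325, and 3.325 − 1.960 = 1.365, which is 91.4% power. The 195 per group left from 230 after 15% dropout have 90.8%. The mismatch between 142 and 199 is a separate matter. Here it sets the starting power at about 91%.

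**Step 2: baseline adjustment against a change score.** With SD s at both visits:

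- Var(change) = 2s²(1 − rho)
- Var(adjusted for baseline) = s²(1 − rho²)
- Ratio = (1 + rho)/2

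The direction does not need equal variances. With SDs s0 and s1, the change-score variance exceeds the adjusted variance by (s0 − rho × s1)², which is never negative. Taking 15 as the SD of change, the adjusted SD is 15 × √ratio:

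| rho (assumed) | Variance ratio | Adjusted SD | n per group for 80% | Power at 199 | 199 / ratio |
|---|---|---|---|---|---|
| 0.3 | 0.65 | 12.09 | 92 | 98.5% | 306 |
| 0.5 | 0.75 | 12.99 | 106 | 97.0% | 265 |
| 0.7 | 0.85 | 13.83 | 121 | 95.0% | 234 |
| 0.8 | 0.90 | 14.23 | 128 | 93.9% | 221 |

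The last column is the number per group that an unadjusted change-score analysis would need to match the precision of an adjusted one with 199.

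**Step 3: centre.** If stratification balances the arms within centres, the true variance of the difference is (1 − ICC) times what the unadjusted test assumes. The actual two-sided type I error is then 2 × [1 − Φ(1.960/√(1 − ICC))], and the SD with centre in the model is 15 × √(1 − ICC):

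| ICC (assumed) | Type I error, centre ignored | Power at 199, centre ignored | Power at 199, centre in model |
|---|---|---|---|
| 0.01 | 0.049 | 91.5% | 91.7% |
| 0.05 | 0.044 | 91.9% | 92.7% |
| 0.10 | 0.039 | 92.5% | 93.9% |

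The error rate stays below 0.05, and the gain from centre is smaller than that from baseline.

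**Step 4: do the other named models already adjust?** Ambulatory monitoring has two time points (Table 1). With two time points, the group-by-time test in a repeated-measures general linear model equals the test on change, so that model adds no baseline adjustment. The mixed-effects model might adjust, but none of its terms is stated.

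**The case against.** **The SAP may hold the model terms.** The article never uses the word unadjusted, an ANOVA can carry a centre factor, and Ethics and Dissemination refers to a statistical analysis plan that is not shown. It stands that adjustment is not ruled out. But the article does not leave the primary method to that plan; it names one, and an analysis following that sentence would use neither variable as a covariate.

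**The primary model is not settled.** The text on missing data refers to a mixed-effects model and to missingness at random as an assumption of the primary analysis, which does not fit a plain two-group ANOVA. This stands, and it is a reason to name one model with its terms.

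**The figures apply to one of two outcomes.** This also stands. The calculation suits the continuous change in the Abstract, which matches the mean-difference sample size. It does not apply to the percentage in the Primary Outcome section.

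**Stronger readings that the documents do not support.**

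- A reader might infer that adjustment lifts power from 80% to about 93%. That requires 15 to be the SD at each visit and rho to be 0.3, giving a change SD of 15 × √1.4 = 17.75, which happens to return 199. The Sample Size section attaches the SD to a difference in the reduction and gives no correlation.
- A reader might infer that ignoring centre makes the test invalid. Step 3 shows it mildly conservative, and randomisation keeps the unadjusted estimate unbiased.
- A reader might infer large centre effects from 17 physicians each titrating in their own way. The Intervention Group and Target Blood Pressure sections set a common decision criterion and common targets, so no size for the centre effect can be drawn from the text.

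**Conclusion.** The point holds as one of efficiency and of matching the analysis to the design. The stated primary ANOVA names neither the stratification factor nor the baseline value that every randomised patient will have. For the continuous outcome, baseline adjustment would give a variance 35% to 10% smaller than a change score, for rho of 0.3 to 0.8. With SD 15 read as the SD of the reduction, power at 199 per arm would go from 91.4% to between 98.5% and 93.9%. Adding centre alone gives at most 1.4 percentage points of power at 199 over the assumed ICC range (92.5% to 93.9% at ICC 0.10).

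These sizes rest on assumed correlations and ICCs and on equal variances at the two visits; only the direction of the baseline gain is free of those assumptions. On the stated SD, power does not fall below 80% for lack of adjustment, so the change is advisable rather than essential to the trial's validity.

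**What to change.** State one primary model: a linear model of month-6 24-hour SBP (or its change) on arm, day-29 24-hour SBP and centre. With baseline in the model, either form of the outcome gives the same arm effect. Centre may be a fixed or a random effect, with small centres pooled by a rule set in advance. Report the adjusted difference with its 95% CI.

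Bring the missing-data text into line: either define the mixed-effects model as this primary model, with its terms, or remove the reference. If the percentage with a 10 mm Hg change is kept as the primary outcome, use the same covariates in an adjusted binary model and drop the ANOVA for that outcome.

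The cost is a few sentences of analysis wording and slightly more analysis work, with no new data. The covariates should be fixed before outcomes are examined by arm, so that they cannot be chosen on the results.

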**Definitions**
Blood pressure load: the percentage of abnormally elevated blood pressure readings, which is usually provided in the ambulatory blood pressure monitoring report. Normal values should be <40% [14,15].Dipping: the difference between the mean systolic pressure during the day and mean systolic pressure during the night. This is expressed as a percentage of the daytime mean, and the accepted normal ranges between 10% and 20% [16].

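### A Shapiro-Wilk test on the trial's own data chooses between a linear model and the Friedman test for before/after comparisons of continuous outcomes, and at about 390 patients it rejects for skew too small to matter

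*Protocol article*

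**What the plan says.** All of this stands in one paragraph of the protocol article, under Statistical Analysis.

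- Normality check: "The normality of continuous data will be assessed with the Shapiro-Wilk test". No separate level is given, so the general rule applies: "All tests will be considered significant at the cutoff value of *P*<.05".
- Route if Gaussian: "we will use a general linear model for repeated measures to compare the marginal means of Gaussian quantitative dependent variables", before and after the intervention.
- Route if not Gaussian: "A nonparametric test (the Friedman test) will be used for the comparison of non-Gaussian quantitative variables before and after intervention".
- Primary end point: "An analysis of variance will be performed to compare the two study groups in terms of the primary end point". No normality condition is attached.
- General comparison of continuous variables: "Differences between continuous variables will be evaluated with a 2-tailed Student" t test or its correction. No normality condition is attached here either, and no rank alternative is named.

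No outcome is assigned to either before/after route in advance. Among the secondary outcomes, blood pressure load and dipping are clearly continuous. Load is defined in the Definitions textbox as "the percentage of abnormally elevated blood pressure readings", so it is bounded between 0% and 100%. SF-12 and most of the blood pressure outcomes are worded as percentages of patients.

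**The concern.** A formal normality test used as a switch behaves badly at this sample size. Its power to detect a departure from normality grows with the number of patients, while the effect of that departure on a comparison of means shrinks. In a trial this large, the test tends to remove the linear model where the model is safe.

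Three things are at stake for the before/after comparisons. The method, and with it the kind of effect reported, is not known until the data are in. Related outcomes such as load and dipping can end up on different scales in the same report. An outcome that fails goes to a Friedman test over time, which has no arm term and gives neither a between-arm difference nor a confidence interval.

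**Working it through.** **Inputs from the article.** Sample Size section: 199 per group for 80% power, difference 5 mm Hg, SD 15 mm Hg, 15% dropout, 230 recruited per group. Allocation is 1:1 (Study Design). Alpha is 0.05; two-sided is stated for the t test.

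**The plan's own figure.** n = 2 × (1.96 + 0.8416)² × 15² / 5² = 141.3, so 142 per group, not 199. With 199 per group the power is Φ(5 / (15 × √(2/199)) − 1.96) = Φ(1.365) = 91%. This mismatch is a separate matter. Here it only explains why the powers below are about 91% rather than 80%.

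**Evaluable patients.** 460 × 0.85 = 391, or about 195 per arm.

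**Step 1: how often the switch fires.** The article gives no distribution for any outcome, so skewness is an assumption and is shown as a range. Data were simulated as gamma with shape k = 4 / skewness², standardised, and tested with Shapiro-Wilk at 0.05. There were 3,000 runs per case (Monte Carlo standard error at most √(0.25/3000) = 0.9 percentage points).

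| Skewness | Rejected, pooled N = 391 | Rejected, one arm (N = 199) |
|---|---|---|
| 0 | 5% | 6% |
| 0.2 | 28% | 16% |
| 0.3 | 55% | 33% |
| 0.4 | 82% | 53% |
| 0.5 | 95% | 72% |
| 0.7 | 100% | 95% |
| 1.0 | 100% | 100% |

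The article does not say whether the test is run pooled or by arm. For comparison, 50 patients at skewness 0.5 give 25% rejection, so the sample size drives the result. For a bounded percentage, assumed beta(1.5, 1.5), beta(2, 1) or beta(1, 1), pooled rejection was 100%.

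**Step 2: whether the skew harms a comparison of means.** Two-sample t test, 195 per arm, SD 15, 40,000 runs per case.

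| Skewness | Type I error | Power for 5 mm Hg |
|---|---|---|
| 0 | 5.1% | 90.6% |
| 0.3 | 4.9% | 90.8% |
| 0.5 | 4.9% | 90.8% |
| 0.7 | 4.9% | 90.6% |
| 1.0 | 4.9% | 90.8% |

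The formula agrees: Φ(5 / (15 × √(2/195)) − 1.96) = Φ(1.33) = 91%. For the beta-shaped data, t-test error was 4.5% to 5.6%.

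**Step 3: where a failing outcome goes.** With two time points, n patients and r of them rising, the Friedman statistic without ties is (2r − n)² / n on 1 degree of freedom. Arm does not appear in it. Assume the same 8 mm Hg fall in both arms, SD of change 15, n = 391. The chance of a rise is Φ(−8/15) = 0.297, so r is about 116.1 and the statistic about (232.2 − 391)² / 391 = 64.5, against a critical value of 3.84. In 2,000 simulated trials with no difference between arms, this test was significant in 100%, and a between-arm rank test in 4%.

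**The case against.** The strongest reply is that the tests that matter most are not switched. This is correct. The primary analysis of variance is stated without a normality condition, and the Gaussian and non-Gaussian terms occur only in the before/after sentences. The Outcomes section also words the primary end point as a percentage of patients, which a normality test cannot reroute. A reader might infer that the headline analysis is left open until the data are seen; the text does not support that.

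The Student t test sentence is also unconditional, so load and dipping could receive a t test whatever Shapiro-Wilk shows. This softens the point without removing it: the article does not say which contrast that test serves, or which result takes precedence.

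A further reply is that pretesting does little damage to error rates. That stands as well. Choosing by Shapiro-Wilk between a t test and a between-arm Mann-Whitney test gave type I error of roughly 4.4% to 5.6% in simulation, and power of 90% to 94% against 90% to 92% for always using t. A claim of inflated false positives would therefore be wrong for that pair. But that is not the pair in the plan, whose rank route is the Friedman test over time.

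Nor can the switch be said to discard a baseline adjustment, since the article specifies none.

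Finally, a separate analysis plan may settle the detail. But the article states a rule rather than leaving one out, and a plan that follows it inherits the problem.

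**Conclusion.** The point holds for the before/after comparisons of continuous outcomes: clearly for load and dipping, and for 24-hour pressure or SF-12 scores only if these are analysed as continuous. At about 391 patients the route is close to chance at skewness 0.3 (55% rejected pooled, about a third within one arm). At skewness 0.5 it leads mostly to the rank test (95% pooled, about 70% within one arm), and for a bounded percentage of the shapes tried it does so in essentially every sample. Throughout, a linear comparison of means keeps about 5% error and 91% power.

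The rule therefore protects against nothing at this size. Its cost is a data-dependent method and effect measure, and a Friedman result that does not compare the arms.

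The percentages rest on assumed gamma and beta shapes; a load distribution closer to bell-shaped would be rejected less often. The change should be made, but the point does not call the primary test into question.

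**What to change.** Remove Shapiro-Wilk as the switch between methods. State that each continuous outcome is analysed with one pre-specified between-arm linear model, for example the 6-month value or the change, adjusted for baseline. Report the mean difference with its 95% confidence interval, using robust or bootstrap standard errors where residuals are skewed. Keep a between-arm rank test for the same outcomes as a labelled sensitivity analysis, in place of the Friedman test.

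The cost is wording in the protocol and the analysis plan; no new data are needed. The one statistical downside is slightly lower power than a rank test for a strongly skewed outcome: about 91% against 94% to 95% at skewness 1.0.
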